## Abstract

**Methods::**

A prospective, randomized and controlled clinical trial will be carried out with coma and intubated patients admitted to the Intensive Care Unit (ICU). Thirty-nine patients will be randomly divided into 3 groups: group who will have the tube inserted in a conventional manner with the head in the neutral position, group with the head positioned laterally to the right, and, finally, with the head in the neutral position, with assistance of a laryngoscope. The primary endpoint will be: first, second and total attempt success rate; and time required for the first successful attempt and the sum of all attempts. Complications during insertion included tube bending, twisting, knotting, mucosal bleeding, and insertion into the trachea. Patient vital signs will be measured.

Strengths and Limitations of this Study•This is a single-center study, and participants will be recruited from a single hospital, which compromises the generalisability of the findings;•Blinding of nurses will not be possible;•The instrument used did not go through the face and content validation process.

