Results favorable to the use of different nasally placed small-bowel feeding tube insertion methods have been described by anesthesiologists.^[11–13]^ Among these, the lateralized head^[5,12]^ and the use of the laryngoscope^[11]^ stand out. Such studies have demonstrated nasally placed small-bowel feeding tube insertion methods that are faster, more effective and that cause less complications to patients. However, it is clear that such techniques are little used by nurses in clinical practice. It is important and necessary for nurses to be able to offer safer care with less risk of complications, based on the best available evidence, through the possibility of revealing the most adequate, effective, fast and safe technique to improve the execution of this procedure.

In a study conducted in Taiwan, 130 insertion attempts were performed. The success rate was 82.7% (86 of 104 patients) on the first attempt and 100% in 5 attempts. In 23 patients the tube deviated to the oral cavity and 3 to the trachea.^[15]^ Verification of vital signs are important to detect clinical deterioration of the patient.^[16]^

We seek to test the following hypothesis: null hypothesis: There are no significant differences between the methods of insertion of the nasally placed small-bowel feeding tube in patients in coma (physiological or induced) and intubated in relation to the rate of success in the first attempt, insertion time and the presence of complications; alternative hypothesis: There are significant differences between the methods of nasally placed small-bowel feeding tube insertion in comatose patients (physiological or induced) and intubated in relation to the rate of success in the first attempt, insertion time and the presence of complications.

Therefore, the study aims to determine the effectiveness of different nasally placed small-bowel feeding tube insertion techniques in coma and intubated patients, in comparison with conventional method.

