### 2.8. Endpoint

#### 1.2.8. Primary outcome.

The success rate on the first attempt will be considered as the dependent variable. Insertion success will be defined as the successful passage of the tube on the first attempt and confirmed by radiography of the correct anatomical positioning of the tube distal tip, which will be performed immediately after the procedure. If the nasally placed small-bowel feeding tube is not successfully inserted, it will be considered a failure and recorded as an unsuccessful attempt. Subsequently, new attempts will be performed.

The number of attempts required for successful insertion will be recorded for each patient. It should be noted that if more than 3 attempts are required, the procedure will be declared unsuccessful and data will be used to count failures. In these cases, the researchers may use another method of free choice for nasally placed small-bowel feeding tube insertion.

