#### 2.2.8. Secondary outcome.

Secondary endpoints will be time required and associated complications. The time required will be recorded from the nasally placed small-bowel feeding tube insertion from the nostril to the calculated length of the tube with the aid of a stopwatch. The insertion times for each attempt will be counted and, in case of failures, the time required for each attempt will be added together.

In addition, AEs associated with the insertion techniques (bleeding of the visible mucosa, nasal mucosa edema, in addition to tube bending, twisting, knotting and insertion into the trachea visible on X-ray) will be recorded. It is noteworthy that the occurrence of bleeding will be considered as visible bleeding in the tube extension and nasal or oral mucosa. The analysis of such AEs will be performed immediately at the end of the procedure until radiological confirmation of the tube positioning and previous removal of the guide wire. The radiograph will be performed on the patient bed and the patient will be kept in the same position, in the supine position. If the patient shows signs of respiratory distress during insertion, the procedure will be stopped.

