### 2.10. Randomization and masking

Thirty-nine patients will be randomly divided into 3 groups. Patients allocated in the control group (CG) will have the tube inserted in the conventional way, that is, the head is kept in the neutral position, while the tube is gently inserted through one of the nostrils, without any maneuver or instrument.

Patients selected for the first intervention group (GI1) will have their heads turned to the right lateral position. This way, the tube will be inserted through the selected nostril without any neck maneuver or instrument.

For patients selected for the second intervention group (GI2), a conventional adult laryngoscope will be orally inserted. The tracheal tube and tongue will be raised to provide the best view of the larynx area. Thus, after viewing the piriform sinus or the esophagus, the tube will be inserted into the patient nostril and advanced to the esophagus under direct visualization. The patient head will be held in the neutral position and the blade will be gently lifted to avoid excessive neck extension.

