### 2.14. Data extraction and statistical analysis

Data will be analyzed using the Statistical Package for Social Science software, version 18.0 (SPSS Version 20.0), where descriptive and inferential analyses will be carried out, and results will be presented through tables, charts and figures. To evaluate variables, the Chi-square test (χ²) or Fisher test or ANOVA will be used. Other statistical tests that may be necessary will also be used. Significance level of 5% (*P* = .05) will be adopted.

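### The abstract names five primary measures and section 2.8 names one; insertion time is primary in the first and secondary in the second, and nothing says which governs

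*Protocol article*

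**What the plan says.** The abstract of the protocol article defines the primary endpoint as "first, second and total attempt success rate; and time required for the first successful attempt and the sum of all attempts". That is three success rates and two times.

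Section 2.8, under the primary outcome heading, says "The success rate on the first attempt will be considered as the dependent variable". The number of attempts, and failure once more than three are needed, are recorded under the same heading but not named as outcomes. The secondary outcome paragraph says "Secondary endpoints will be time required and associated complications".

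The Introduction states null and alternative hypotheses "in relation to the rate of success in the first attempt, insertion time and the presence of complications", without labelling any of the three as primary.

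Section 2.14 says "To evaluate variables, the Chi-square test (χ²) or Fisher test or ANOVA will be used", then "Other statistical tests that may be necessary will also be used", and closes with "Significance level of 5% (*P* = .05) will be adopted". It ties no test to a named endpoint and gives no order among endpoints. Section 2.9 gives an effect size, power and significance level but no outcome. The Introduction's stated aim is to compare the techniques with the conventional method.

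**The concern.** The two definitions are incompatible. Insertion time is primary in the abstract and secondary in section 2.8. Second-attempt and total success are primary in the abstract and have no stated rank in section 2.8. An analysis plan outside this article could add detail, but it would not remove the contradiction within it.

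A report that followed the abstract could present any of five measures as the primary result and cite the protocol in support. Section 2.1 says that data collection is under way, and section 2.6 says that only the data analysts are blinded, so the choice needs to be fixed before results by arm are examined. With 39 patients in three arms, chance differences on one measure or another are easy to find. What is at stake is the error rate of the primary claim.

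**Working it through.** **1. The passages side by side**

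| Measure | Abstract | Section 2.8 | Hypothesis (Introduction) |
|---|---|---|---|
| First-attempt success | primary | primary | listed, no rank |
| Second-attempt success | primary | no rank stated | not listed |
| Total success | primary | no rank stated | not listed |
| Time, first successful attempt | primary | secondary (time) | listed as insertion time, no rank |
| Time, all attempts summed | primary | secondary (time) | listed as insertion time, no rank |
| Complications | listed apart from the primary endpoint | secondary | listed, no rank |

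The abstract and section 2.8 agree on the first row only. The hypothesis lists section 2.8's primary outcome followed by its two secondary ones.

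**2. Does the sample size identify the endpoint?** Section 2.9 gives a Cohen effect size of 0.80, power 0.80 and 5%, and arrives at 39. It names neither the outcome nor the effect-size index. The usual readings give:

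- three-arm chi-square (w = 0.8, 2 df): 16
- three-group ANOVA (f = 0.8): 21
- two-sided t-test, 1:1 (d = 0.8): 52

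None is 39. A chi-square with w = 0.5 and 2 df does give 39, but 0.5 is not the stated effect size. So the calculation does not show which endpoint the trial was sized for.

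**3. Size of the problem if all five measures are primary.** The plan gives no figure of its own to reproduce here.

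- If the five were independent, each with one test at 5%: 1 − 0.95^5 = 1 − 0.774 = 0.226, or 23%.
- They are not independent. The three success rates overlap, and summed time rises with the number of failed attempts. A null simulation allowed for this. It used three arms of 13 (39/3), up to three attempts per patient, and the same per-attempt success probability in every arm. Second-attempt and total success were taken as success by the second and by the third attempt, and times were lognormal. Each endpoint had one three-arm test (chi-square for success, ANOVA for time), with 3,000 runs per setting.

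| Assumed success per attempt | First-attempt success alone | At least one of five |
|---|---|---|
| 0.50 | 4.6% | 16.2% |
| 0.70 | 5.8% | 15.7% |
| 0.827 | 4.4% | 11.9% |

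The value 0.827 is the first-attempt rate the Introduction cites from a study in Taiwan (86/104); the other two are assumptions. The simulation error is about √(0.16 × 0.84/3000) = 0.007. The result is therefore roughly 12-16% with five primary measures, against about 5% with one.

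**4. Would a gated analysis hold the error rate on the single endpoint?** There are two hypotheses of interest: CG equals GI1, and CG equals GI2. Their intersection is that all three arms are equal, which is what the three-arm test examines. Testing that at 5% first, and each contrast at 5% only if it is rejected, is a closed procedure. It holds the familywise error at 5% without splitting alpha, provided each component test holds its own 5% level.

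**The case against.** The strongest reply is that section 2.8 is the operative text, that its primary outcome heading names one variable, and that the abstract is loose summary wording. Much of this stands, and the fix adopts section 2.8. But the article nowhere says that section 2.8 prevails, and the abstract states its list as a definition.

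A reader might infer several stronger charges that the document does not support:

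- **That the hypothesis is a third, rival definition with three primary outcomes.** It calls none of them primary, and it matches section 2.8's primary outcome plus its two secondary ones.
- **That every endpoint and contrast will be tested unadjusted at 5%.** Section 2.14 gives one general level. Corrections and the mapping of tests to endpoints are commonly left to a fuller document, so their absence here is no finding.
- **That only overall three-group tests are planned.** Section 2.14 does not say so, and chi-square and Fisher tests also serve for two-arm contrasts. Nor can a true GI1 v GI2 difference exist alone: if those two differ, at least one differs from CG. Only the observed P-values can show that pattern.
- **That the inflation is 23% or 26%.** The first assumes five independent endpoints. The second (1 − 0.95^6, two control contrasts on three outcomes) also treats contrasts sharing one control arm as independent.
- **That unadjusted contrasts on the single primary endpoint give 9% (two against control) or 12% (three pairwise).** Those are normal-approximation values. Enumeration at 13 per arm gives 2-5% for two control contrasts with Fisher's test and 7-13% with uncorrected chi-square, so the answer depends on the test chosen.

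A further objection is that gating costs power. With 13 per arm and assumed true success of 0.50 v 0.90 v 0.90, an exact global test followed by Fisher contrasts finds a difference from control 61% of the time; with 0.50 v 0.827 v 0.827 it is 39%. Both fall short of the 80% in section 2.9. That is fair to record, but most of the shortfall comes from the arm size: ungated Fisher contrasts do only slightly better.

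**Conclusion.** The point holds as a contradiction between the abstract and section 2.8 over what is primary, which the sample-size paragraph does not resolve. If the abstract is followed, the chance of at least one false-positive primary result is roughly 12-16% rather than 5%.

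That range assumes 13 patients per arm, one three-arm test per endpoint, equal per-attempt success of 0.50 to 0.827 and lognormal times. Equal arms are themselves an assumption, because the split in section 2.9, read literally, adds to 13 + 26 + 26 = 65 rather than 39. If section 2.8 is followed with one three-arm test of first-attempt success, the inflation disappears (4.4-5.8% in the same simulation). It would go too far to say that the trial has no identifiable primary outcome: section 2.8 names one, and the defect is that the abstract contradicts it.

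**What to change.** 1. Correct the abstract to match section 2.8: first-attempt success is the single primary endpoint. List second-attempt and total success, both times and complications as secondary, reported without confirmatory claims. Give second-attempt and total success the same rank in section 2.8.
2. In the Introduction, mark first-attempt success as the primary one of the three outcomes in the hypothesis. The other two can stay.
3. In section 2.14, state that the primary analysis is the three-arm test of first-attempt success at 5% and, only if it is significant, CG v GI1 and CG v GI2 at 5% each. The stated aim is comparison with the conventional method, so these are the contrasts that answer it.
4. Name the outcome in section 2.9 to which the sample size refers.
5. Date the change and make it before results by arm are examined, since data collection is ongoing.

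The cost is wording in four places. The downside is that time and later-attempt success can no longer be claimed as primary results, and the gated contrasts lose a little power against unadjusted ones.

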## 1. Introduction

According to the World Health Organization, 1 in 10 patients experience unnecessary harm as a consequence of unsafe health care assistance, which in more extreme situations, can cause the patient death.^[1]^ In this context, patient safety is related to a set of activities that aim to mitigate risks to an acceptable minimum, make the error less likely and, when it occurs, reduce the impact^[2]^ prevents the occurrence of adverse events (AEs) or injuries resulting from health procedures.^[3]^

In this context, despite being a common procedure, nasally placed small-bowel feeding tube insertion is not risk-free and can compromise patient safety. Due to the fact that nasally placed small-bowel feeding tube is commonly inserted ‘“blindly,” with the patient head in the neutral position, sometimes the process becomes difficult and traumatic, and may present higher level of complexity in physiological or induced coma and intubated patients, as the tongue displaced backwards blocks the passage through the pharynx. In addition, the piriform sinus and the arytenoid cartilage are considered anatomical obstacles for the nasally placed small-bowel feeding tube passage, which is sometimes bended in the oral cavity due to the inability to swallow and the presence of the endotracheal cannula cuff.^[4]^

Therefore, AEs such as accidental tube displacement, wrong positioning in the respiratory tract, tube obstruction, inadvertent exit, bronchoaspiration and connection route errors can occur during this procedure.^[5,6]^ Among serious and fatal AEs, pneumothorax, aspiration pneumonia and pulmonary hemorrhage stand out.^[7,8]^

There are different nasally placed small-bowel feeding tube insertion methods in critically ill and/or coma patients, which, although less common, have high procedural success rates, but none of them is perfect or universally accepted.^[9,10]^ It is noteworthy that the choice of techniques for this study was based on high success rate, low cost, availability and the lack of need to remove the patient from the Intensive Care Unit (ICU).^[11–14]^

Results favorable to the use of different nasally placed small-bowel feeding tube insertion methods have been described by anesthesiologists.^[11–13]^ Among these, the lateralized head^[5,12]^ and the use of the laryngoscope^[11]^ stand out. Such studies have demonstrated nasally placed small-bowel feeding tube insertion methods that are faster, more effective and that cause less complications to patients. However, it is clear that such techniques are little used by nurses in clinical practice. It is important and necessary for nurses to be able to offer safer care with less risk of complications, based on the best available evidence, through the possibility of revealing the most adequate, effective, fast and safe technique to improve the execution of this procedure.

In a study conducted in Taiwan, 130 insertion attempts were performed. The success rate was 82.7% (86 of 104 patients) on the first attempt and 100% in 5 attempts. In 23 patients the tube deviated to the oral cavity and 3 to the trachea.^[15]^ Verification of vital signs are important to detect clinical deterioration of the patient.^[16]^

We seek to test the following hypothesis: null hypothesis: There are no significant differences between the methods of insertion of the nasally placed small-bowel feeding tube in patients in coma (physiological or induced) and intubated in relation to the rate of success in the first attempt, insertion time and the presence of complications; alternative hypothesis: There are significant differences between the methods of nasally placed small-bowel feeding tube insertion in comatose patients (physiological or induced) and intubated in relation to the rate of success in the first attempt, insertion time and the presence of complications.

Therefore, the study aims to determine the effectiveness of different nasally placed small-bowel feeding tube insertion techniques in coma and intubated patients, in comparison with conventional method.

## 2. Methods

### 2.1. Study design

This is a single center study protocol for a randomized clinical trial to evaluate the effectiveness of different nasally placed small-bowel feeding tube insertion techniques in coma and intubated patients, in comparison with conventional method. This study will adhere to the Standard Protocol Items for Randomized Trials^[17]^ and the Consolidated Standards of Reporting Trials.^[18]^ The data collection stage is ongoing.

### 2.2. Study setting

Recruitment will be from patients admitted in an ICU of a tertiary hospital from the state of Rio Grande do Norte, Brazil.

### 2.3. Population

Physiological or induced coma and intubated patients admitted to the ICU in will be included.

### 2.4. Eligibility criteria

The study will include patients in physiological coma (score between 3 and 8 on the Glasgow Coma Scale) or induced coma (score between 5 and 6, slow response to stimuli and deep sedation, respectively), on the Ramsay scale, submitted to invasive mechanical ventilation, indication of nasoenteral tube under medical prescription, aged 18 years or older. It is noteworthy that patients who lost the nasoenteral tube due to inadvertent exit or obstruction will also be included.

Exclusion criteria were: patients with coagulopathy (abnormal prothrombin time, partial thromboplastin time and platelet disorders); nasal stenosis; upper respiratory tract anomalies; esophageal disorders (esophageal hiatus hernia, esophageal varices, esophageal or nasopharyngeal carcinoma); skull base fracture; teeth with mobility and history of difficult intubation. In order to verify such information, medical records were consulted before the procedure was performed.

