### 2.5. Recruitment

The study flowchart is described in Figure 1. Patients will be recruited upon the need for nasoenteral tube insertion the ICU. At the opportunity, the eligibility criteria for participation in the research will be applied. Subsequently, as critical patients admitted to the ICU are unable to consent, consent will be obtained from legal guardians prior to the intervention. Each research participant will have to fill out the Free Informed Consent Form, with the reading and signature of the respective family member legally responsible for the patient.

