### 2.7. Intervention

In all patient groups, a 120 cm 12 French gauge (1 French = 0.33 mm) nasally placed small-bowel feeding tube was standardized for use in the institution where the study will be carried out. The length of the tube needed to reach the jejunum will be assessed prior to insertion and measured by placing the nasally placed small-bowel feeding tube from the earlobe to the xiphoid process and then down to the umbilicus (EXU method).^[19]^ Before insertion, 3 milliliters of 2% xylocaine will be applied to the patient nostril, selecting the one with no nasal obstruction or deviated septum. In each group, the nasally placed small-bowel feeding tube will be passed through the patient nostril, posteriorly along the floor of the nose and advanced to reach the measured length.

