### 2.11. Data collection

A data collection printed form containing variables about patients will be used, namely: Identification (bed; name initials; age; sex; date of birth); Clinical data (cause of admission; estimated weight, height and body mass index); Level of consciousness or Ramsay scale data, including type of drug used and sedation duration; Endotracheal tube number and cuff pressure; Data regarding the technique used (technique; number of attempts; required time in seconds; complications, if any); Parameters to be evaluated (heart and respiratory rate, blood pressure and oxygen saturation) before, during and after nasally placed small-bowel feeding tube insertion using each of the techniques; Confirmation of the correct nasally placed small-bowel feeding tube positioning by chest and abdomen radiography in bed.

Table 1 shows the detailed study stages, with the Standard Protocol Items for Randomized Trials schedule of enrollment, interventions, and assessments.

**Table 1 T1:** Description of the study stages: P1: Day 1—request for nasally placed small-bowel feeding tube insertion in the patient and intervention. F1: evaluation after the procedure until X-ray is performed.

Study period					
			Post-allocation: Allocation, interventions, follow-up		
Timepoint	Enrollment	Baseline	Allocation	P1 intervention	Follow-up (F1)
Enrollment:					
Eligibility criteria	X				
Recruitment	X				
Initial assessment	X				
Informed consent	X				
Allocation			X		
Interventions:					
Insertion in a conventional manner (control group)				⟷	X
Insertion with the head turned to the right side (intervention group)				⟷	X
Insertion with laryngoscope (intervention group)				⟷	X
Assessments:					
Identification, clinical data, level of consciousness, SSVV, among others		X			

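### Bleeding and edema are scored only after insertion in a sample that includes replacement insertions, so trauma from an earlier tube can be counted as a complication in any arm

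*Protocol article*

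**What the plan says.** **Who enters.** Section 2.4 admits patients who need a tube and adds that "patients who lost the nasoenteral tube due to inadvertent exit or obstruction will also be included". The exclusions end with "teeth with mobility and history of difficult intubation". None of them concerns a recent insertion or an existing injury of the nasal or oral mucosa.

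**What is checked beforehand.** Section 2.7 chooses the nostril by "selecting the one with no nasal obstruction or deviated septum". Bleeding and edema are not mentioned.

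**What is scored.** The Secondary outcome part of 2.8 lists, among the adverse events associated with the techniques, "bleeding of the visible mucosa, nasal mucosa edema". Bleeding means any that is visible along the tube or on the nasal or oral mucosa. Assessment runs from the end of the procedure to radiological confirmation.

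**What is recorded.** Section 2.11 itemises the form. The part on the procedure reads "Data regarding the technique used (technique; number of attempts; required time in seconds; complications, if any". No item covers first versus replacement insertion, the nostril used, or the mucosa before insertion. Vital signs, by contrast, are taken before, during and after.

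**The concern.** The inclusion rule, the event definition and the form do not fit together. A patient whose previous tube came out or blocked may already have a swollen or bleeding nose. Applied as written, the definition counts that finding as an event of the newly assigned technique, and the listed data give no means of separating old from new.

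Complications are one of the three components of the hypotheses in the Introduction, so this touches a stated comparison. Three things are at stake:

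- the absolute rates of bleeding and edema would be too high;
- true differences between techniques in these two items would look smaller;
- with few patients per arm, an uneven spread of replacement insertions could create or hide a difference.

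**Working it through.** The article gives no figure for the share of replacement insertions, for residual mucosal signs or for expected complication rates, so there is no plan figure to reproduce. The values below are assumptions, shown over a range.

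**Inputs**
- q, the share of participants with an earlier tube: 20% or 40% (assumed).
- t, the share of those with visible bleeding or edema before the new insertion: 10% or 30% (assumed).
- p, the true rate of new bleeding or edema: 10% in one arm, 30% in another (assumed).
- Arm size 13, from 39/3. This is also an assumption: 2.9 gives 13 controls and 26 to each intervention group, and 13 + 26 + 26 = 65, not 39. That conflict is a separate matter.

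**Step 1. Inflation and dilution with perfectly balanced arms.** If old signs and new events occur independently, the recorded rate is

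recorded = 1 − (1 − p)(1 − q·t).

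The recorded difference between two arms is the true difference times (1 − q·t).

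| q | t | q·t | true 10% recorded as | true 30% recorded as | 20-point difference becomes |
|---|---|---|---|---|---|
| 20% | 10% | 0.02 | 11.8% | 31.4% | 19.6 |
| 20% | 30% | 0.06 | 15.4% | 34.2% | 18.8 |
| 40% | 10% | 0.04 | 13.6% | 32.8% | 19.2 |
| 40% | 30% | 0.12 | 20.8% | 38.4% | 17.6 |

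Last row in full: 1 − 0.90 × 0.88 = 0.208; 1 − 0.70 × 0.88 = 0.384; 0.384 − 0.208 = 0.176. A low true rate is distorted most: 10% roughly doubles, while the contrast between arms loses 12% of its size.

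**Step 2. Chance imbalance.** The number of prior-tube patients in each of three arms of 13 was simulated as binomial (200,000 replicates). The probability that the largest and smallest counts differ by 4 or more is:

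| assumed share with an earlier tube | probability |
|---|---|
| 10% | 0.05 |
| 20% | 0.19 |
| 30% | 0.29 |
| 50% | 0.35 |

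**Step 3. What such an imbalance does.** Take two arms with the same true rate of 10% that differ by 4 of 13 prior-tube patients. The expected spurious difference is (4/13) × t × (1 − p):
- t = 30%: 0.308 × 0.30 × 0.90 = 0.083, about 8 points;
- t = 10%: 0.308 × 0.10 × 0.90 = 0.028, about 3 points.

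The sign depends on which arm happens to hold more of these patients.

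**The case against.** **The form may hold more than the article lists.** The printed form is not shown, and the baseline row of Table 1 is open-ended. Medical records are consulted before the procedure (2.4) and original documents are kept for 15 years (2.12), so insertion type may be recoverable. This stands, and it rules out saying that an imbalance could never be checked. It helps less with mucosal state, which may not be recoverable unless someone notes it at the bedside. Nor does it change the event definition, which the article states.

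**Partial safeguards exist.** Choosing an unobstructed nostril works against using a badly swollen one, and coagulopathy is excluded. Both reduce the problem. Neither covers residual bleeding, non-obstructing edema or the oral mucosa.

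**A reader might infer a bias against the new techniques.** The documents do not support that. Replacement patients can fall in all three arms, and randomisation balances them in expectation. What remains is inflation, dilution and chance imbalance.

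**A reader might infer that first-attempt success is distorted too.** The article gives nothing from which to show this. Bending, twisting, knotting and tracheal insertion also have no evident carry-over.

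**A reader might infer that one patient can be randomised twice, so that records are not independent.** Section 2.5 says "Patients will be recruited upon the need for nasoenteral tube insertion", but not at each need, and 2.10 says "Thirty-nine patients will be randomly divided into 3 groups". The counted and randomised unit is the patient throughout. The article does not state whether a patient can be randomised again, and a once-only rule is the kind of detail that a full protocol holds. Silence here is not a shown error.

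**Conclusion.** The point holds for two items of a secondary outcome, visible bleeding and nasal edema. Patients with an earlier tube are deliberately admitted, and these findings are scored afterwards without a stated baseline, so earlier trauma can be misclassified as a complication of whichever technique is assigned.

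The effect is modest and has no fixed direction. At the upper end of the assumed range, the recorded rates rise by 8 to 11 points and a 20-point contrast loses about 2; at the lower end, the change is under 2 points. Chance imbalance could add a spurious difference of about 3 to 8 points when arms of 13 differ by four prior-tube patients. All of this rests on assumed prevalences and equal arms, since the article supplies neither replacement rates nor complication rates. It is a worthwhile, cheap improvement and does not threaten the primary outcome.

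**What to change.** 1. Add two fields completed before insertion: first or replacement insertion, and whether bleeding or edema is already visible in the nose (noting the chosen nostril) or mouth, with enough description to judge later worsening.
2. In the Secondary outcome definition, count bleeding or edema as a complication only if new or worsened relative to that check.
3. Report the number of replacement insertions by arm.

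The cost is two bedside fields and one amended definition. Section 2.1 says that data collection is ongoing, so the fields will be missing for patients already enrolled. Insertion type might be sought in their records, and the report should say how many patients have the baseline check.

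As a clarification only, one sentence could state that each patient is randomised once.
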